**3.11 Allocation concealment mechanism and blinding**

The treatment allocation for each household would be kept in the community health department until the study sites has completed training and are ready to implement the intervention. Clusters would be identified and recruited before randomisation. All eligible patients within the cluster would be included in the study. Allocation would be concealed from the community health nurses and family head who gave consent for household to be included in the trial. Also, allocation sequence would be concealed from researchers/clinicians enrolling and assessing participants. Sequence would be concealed in a sequentially numbered, opaque sealed and stapled envelopes. Corresponding envelopes would be opened only at the time of allocation of intervention. The intervention would be prepacked and correspond to the study arm assigned to. Independent clinicians that would assess outcome would be kept blind to intervention assignment of the household.

**3.12 Outcome measures**

Outcome measures mainly pertain to individual participant level. The study will evaluate the effect of LAD interventions on the prevalence of anaemia in the study arm.

***3.12.1 Primary outcome***

The primary outcome measures are mean haemoglobin levels and prevalence of anaemia in study arms. The haemoglobin level would be measured using a haematological analyser that measures the full (complete) blood count. Haemoglobin would be measured at baseline and end of intervention. Mean haemoglobin concentration (Hb g/dL) and prevalence of anaemia in children: Hb <11.0 g/dL; mild anaemia (10.0 g/dL ≥ Hb ≤ 10.9 g/dL), moderate anaemia (7.0 g/dL ≥ Hb ≤ 9.9 g/dL), and severe anaemia as Hb < 7.0 g/dl would be determined at baseline and at end of intervention.

**3.12.2 Secondary outcome**

A number of secondary outcomes would be measured in this study. Secondary outcomes would include measurement of anthropometry, and dietary recall, serum iron, ferritin, and other parameters of full blood count.

***3.12.2.1 Anthropometric Measures: Physical growth***

Secondary outcomes pertaining to child physical development would be measured and compared among study arms. The change in prevalence of underweight (weight-for-age, Z-score <−2), wasting (weight-for-height, Z-score <−2), stunting (length/height-for-age, Z-score <−2) and Mid Upper Arm circumference (MUAC) for age would be measured. Others measures include head circumference for age, and body fat composition estimates using triceps skin fold thickness (TSF) for age and subscapular skin fold (SSF) for age. Body weight would be measured to the nearest gram using a battery powered digital scale; it would be measured under standardized conditions (patients dressed in underclothes, barefoot, and with an empty bladder). Height or length would be measured using stadiometer or infantometer to the nearest millimetre. Height would be obtained for children above 2 years and length for children below 2 years. Head circumference would be measured using a flexible non-elastic tape measure. The tape measure would be wrapped snugly around the widest possible diameter of the forehead; about 1-2 fingers above the eyebrow to the widest part of the back of the head.

The MUAC is the circumference of the left upper arm. The following steps would be employed to measure it: Bend the left arm, and find the mid-point between the olecranon process and acromion. With the arm hanging straight down, a MUAC tape would be wrapped around the arm at the midpoint mark. MUAC would be measured to the nearest 1 mm. Triceps and subscapular skinfold thickness would be measured from the left side of the body to the nearest 1 mm using a skinfold calliper at the following sites: triceps skin fold, halfway between the acromion process and the olecranon process. The subscapular skinfold thickness, would be measured approximately 20mm below the tip of the subscapular skinfold. All anthropometric measurement would be measured twice and the average taken. The WHO growth standards Z scores provide a technically robust set of tools to describe the growth of children under five years of age. Its development involved studies in six countries of which Ghana was among. This makes it ideal for use in Ghanaian population hence it would be the reference chart used for all anthropometric measurement.

***3.12.2.2 Biochemical outcome measures***

The main biochemical measure would be the serum ferritin for all the study participants at baseline and at the end of the intervention period. Serum ferritin levels would be measured using a chemistry analyser employing immunoturbidimetric assay method and would be reported in micrograms per litre. Serum iron concentration and serum transferrin saturation would also be determined. Serum Vitamin B12 and serum folate levels will also be determined at baseline and at end of the intervention period.

***3.12.2.3 Clinical assessment***

Clinical assessment would be carried out at baseline and at the end of the study. It would include a general examination; oedema, pallor, jaundice, skin colour and hair changes. Systemic examination conducting cardiovascular, respiratory and abdominal examinations would be carried out looking out for abnormalities on examination. Other specific examination for micronutrient deficiency would be carried out. For vitamin A deficiency; night blindness, Xerophthalmia, conjunctival xerosis, corneal ulceration, keratomalica. A clinical assessment checklist would be used to capture data regarding clinical assessment. A clinical diagnosis of nutritional status would be made for each study participant.

**3.12.2.4 Dietary recall and quantification of dietary content of micronutrients**

A monthly 24-hour dietary recall would be measured for all study participants. It would be structured to provide requisite information for quantifying the World Health Organization indicators for assessing the quality of infant and young child feeding which include: timely introduction of complementary foods; frequency of feeding; diversity; both frequency and diversity); intake of vitamin A–rich foods; and intake of iron-rich foods. The above is expanded to include the locally available food rich in enhancers and inhibitors of iron absorption. It will also estimate the content of vitamin B12, and folate in the diet using the aid of a food composition tables and detail 24 hour recall [73]. The 24-hour recall would also have a section that estimate the recipes in the locally available food taken so as to obtain a fairly representative content of micro nutrients in the meals eaten. It will be structured to also determine nutrient adequacy ratios of meals in the 24hour dietary recall.

**3.12.2.5 Other haematological measures**

Other haematological indices such as mean corpuscular haemoglobin (MCH), mean corpuscular volume (MCV), Mean corpuscular haemoglobin concentration (MCHC) will be measured. The white blood cell count and its differentials would be obtained in a complete blood count test.

***3.12.2.8 Household food insecurity access scale (HFIAS) for measurement of food Access***

Household food insecurity may be a confounder that may influence adoption of behavioural change communication intervention promoting intake of enhancers of iron absorption and discouraging the intake of inhibitors of iron absorption. A nine-item food insecurity scale, HFIAS developed by the USAID’s FANTA project [74], as a universal measure of food insecurity would be used. The instrument has measures that begins with anxiety about food supply, decrease in quality of food, decrease in quantity of food, going to sleep hungry, and going all day and all night without food. It is scored on a scale of 0 to 27 where a higher number means a household experience more food insecurity. The assessment would be carried out at baseline and the end of the intervention.

**3.12.2.9 Household dietary diversity score**

Household dietary diversity score (HDDS) is a Food and Nutrition Technical Assistance (FANTA) III project that measures the number of food groups consumed over a given reference period [75, 76]. Dietary diversity is a qualitative measure of food consumption that reflects household access to a variety of foods, and is also a proxy for nutrient adequacy of the diet of individuals. It is an important indicator that describe the diversity of diet consumed by a household or individual in the past 24hours. This study would use the dietary diversity tool in relation to individual level. Dietary diversity scores have been validated for several groups as a proxy measure for macro and micronutrient adequacy of the diet. A more diversified diet has been associated with a number of improved outcomes in child anthropometric status, improved haemoglobin concentration and developmental scores. The data is collected by asking the respondent a series of yes or no questions addressed to the person in charge of food preparation. ‘No’ is scored ‘zero’ and ‘yes’ scored ‘one’. The sum of the HDDS ranges from 0 to 12. The mean HDDS would be computed per study arm at baseline and at the end of the intervention. Appendix 4 shows the HDDS study tool.

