**Table 3.1 Baseline and Outcome measures, intermediary factors and time points**

| **Primary and Secondary outcomes** | | **Baseline** | **Week** | | **End-line** |
| --- | --- | --- | --- | --- | --- |
|  |  | **Week 0** | **4** | **8** | **Week 12** |
| **Primary outcome** | |  |  |  |  |
| 1 | Haemoglobin concentration | X |  |  | X |
|  | Anaemia prevalence | X |  |  | X |
| **Secondary Outcomes** | |  |  |  |  |
| **2** | **Anthropometry** |  |  |  |  |
|  | Weight | X |  |  | X |
|  | Length/Height | X |  |  | X |
|  | Mid Upper Arm Circumference | X |  |  | X |
| **3** | **Biochemical outcome** |  |  |  |  |
|  | Serum Ferritin | X |  |  | X |
|  | Serum Iron concentration | X |  |  | X |
|  | Serum transferrin saturation | X |  |  | X |
|  | Serum Vitamin B12 level | X |  |  | X |
|  | Serum folate | X |  |  | X |
|  |  |  |  |  |  |
| **4** | **Clinical Outcome** |  |  |  |  |
|  | ***General Examination*** |  |  |  |  |
|  | Oedema | X |  |  | X |
|  | Jaundice | X |  |  | X |
|  | Pallor | X |  |  | X |
|  | Skin and hair changes | X |  |  | X |
|  |  |  |  |  |  |
| **5** | **Dietary recall and quantification** |  |  |  |  |
|  | 24 hour dietary recall | X |  |  | X |
|  | Enhancers of iron in diet | X | X | X | X |
|  | Inhibitors of iron in diet | X | X | X | X |
| **6** | **Household food insecurity access scale (HFIAS)** | | |  |  |
|  | Household food insecurity | X |  |  | X |
| **7** | **Household dietary diversity score (HDDS)** |  |  |  |  |
|  | Administered at individual level | X | X | X | X |
| **8** | **Household Questionnaire** |  |  |  |  |
|  | Demographic data | X |  |  |  |
|  | Socioeconomic status | X |  |  |  |
| **9** | **Adherence to Study medication** |  | **X** | **X** | **X** |

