Appendix 4: Household dietary diversity questionnaire

| ***DIETARY DIVERSITY QUESTIONNAIRE*** | | | | | | | | |
| --- | --- | --- | --- | --- | --- | --- | --- | --- |
| **Please describe the foods (meals and snacks) that you ate or drank yesterday during the day and night, whether at home or outside the home. Start with the first food or drink of the morning.** | | | | | | | | |
| *Write down all foods and drinks mentioned. When composite dishes are mentioned, ask for the list of ingredients*  *When the respondent has finished, probe for meals and snacks not mentioned.* | | | | | | | | |
| **Breakfast** | | **Snack** | **Lunch** | | **Snack** | **Dinner** | **Snack** | |
|  | |  |  | |  |  |  | |
| *When the respondent recall is complete, fill in the food groups based on the information recorded above. For any food groups not mentioned, ask the respondent if a food item from this group was consumed.* | | | | | | | | |
| **Question number** | **Food group** | | | **Examples** | | | | **YES=1 NO=0** |
| 1 | CEREALS | | | corn/maize, rice, wheat, sorghum, millet or any other grains or foods made from these (e.g. bread, noodles, porridge or other grain products) + *insert local foods e.g. porridge or pastes* | | | |  |
| 2 | WHITE ROOTS AND TUBERS | | | white potatoes, white yam, white cassava, or other foods made from roots | | | |  |
| 3 | VITAMIN A RICH VEGETABLES AND TUBERS | | | pumpkin, carrot, squash, or sweet potato that are orange inside + *other locally available vitamin A rich vegetables (e.g. red sweet pepper)* | | | |  |
| 4 | DARK GREEN LEAFY VEGETABLES | | | dark green/leafy vegetables, including wild forms + *locally available vitamin A rich leaves such as amaranth, cassava leaves, kale, spinach* | | | |  |
| 5 | OTHER VEGETABLES | | | other vegetables (e.g. tomato, onion, eggplant) + *other locally available vegetables* | | | |  |
| 6 | VITAMIN A RICH FRUITS | | | ripe mango, cantaloupe, apricot (fresh or dried), ripe papaya, dried peach, and 100% fruit juice made from these + *other locally available vitamin A rich fruits* | | | |  |
| 7 | OTHER FRUITS | | | other fruits, including wild fruits and 100% fruit juice made from these | | | |  |
| 8 | ORGAN MEAT | | | liver, kidney, heart or other organ meats or blood-based foods | | | |  |
| 9 | FLESH MEATS | | | beef, pork, lamb, goat, rabbit, game, chicken, duck, other birds, insects | | | |  |
| 10 | EGGS | | | eggs from chicken, duck, guinea fowl or any other egg | | | |  |

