| 11 | FISH AND SEAFOOD | | | fresh or dried fish or shellfish | | | |  |
| 12 | LEGUMES, NUTS AND SEEDS | | | dried beans, dried peas, lentils, nuts, seeds or foods made from these (eg. hummus, peanut butter) | | | |  |
| 13 | MILK AND MILK PRODUCTS | | | milk, cheese, yogurt or other milk products | | | |  |
| 14 | OILS AND FATS | | | oil, fats or butter added to food or used for cooking | | | |  |
| 15 | SWEETS | | | sugar, honey, sweetened soda or sweetened juice drinks, sugary foods such as chocolates, candies, cookies and cakes | | | |  |
| 16 | SPICES, CONDIMENTS, BEVERAGES | | | spices (black pepper, salt), condiments (soy sauce, hot sauce), coffee, tea, alcoholic beverages | | | |  |
| Individual level | Did you eat anything (meal or snack) OUTSIDE the home yesterday? | | | | | | |  |

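### The dietary diversity score is stated to run 0 to 12, but its 16-item tool gives 0 to 16 as scored, and the questions ask what the food preparer ate, not the child

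*Protocol*

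**What the plan says.** Section 3.12.2.9 gives the scoring rule. A no answer "is scored ‘zero’ and ‘yes’ scored ‘one", the items are added, and "The sum of the HDDS ranges from 0 to 12". It names the instrument: "Appendix 4 shows the HDDS study tool". The mean is to be reported for each arm at baseline and at the end of the intervention.

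Appendix 4 has a single yes/no column coded 1 and 0 against numbered food groups. The last, item 16, is "SPICES, CONDIMENTS, BEVERAGES". A further unnumbered row asks about eating outside the home. Neither the appendix nor section 3.12.2.9 says that any items are combined before summing.

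On whose diet is meant, section 3.12.2.9 says "This study would use the dietary diversity tool in relation to individual level", and Table 3.1 repeats "Administered at individual level" for weeks 0, 4, 8 and 12. Section 3.4 defines participants as children aged 6 to 56 months. Section 3.12.2.9 directs the questions to whoever is in charge of preparing food, and the form opens with "Please describe the foods (meals and snacks) that you ate or drank yesterday during the day and night".

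**The concern.** Two things do not fit together.

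The first is the scale. A team that follows the text exactly will obtain scores above the stated maximum. A team that aims for the stated maximum must devise a merging rule. The two scores respond differently to the same change in diet, and the items that would be merged are vegetables, fruits and meats, which the dietary guide in Table 3.2 promotes.

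The second is the subject. If the form is used as printed, the answers describe the adult respondent. Section 3.2 makes children the unit of analysis, so siblings with the same respondent would each be given that adult's score. A scoring rule can be settled after the data are in, provided the items are stored. Answers about the wrong person cannot be converted later into answers about the child.

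**Working it through.** **Inputs.** Scoring rule and stated range: section 3.12.2.9. Items: Appendix 4. Level of measurement: section 3.12.2.9 and Table 3.1. Participants: section 3.4.

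**1. The plan's own figure.** The stated maximum is 12. Under the stated rule the maximum equals the number of yes/no items. Appendix 4 has items 1 to 10 (cereals through eggs) and items 11 to 16 (fish through spices, condiments and beverages):

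10 + 6 = 16, so the range is 0 to 16.

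Counting the outside-home question as well would give 16 + 1 = 17. Neither count reproduces 12.

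**2. What would reproduce 12.** Assume that related items count once: vegetables (items 3 to 5, three into one), fruits (items 6 and 7, two into one) and meats (items 8 and 9, two into one):

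16 − 2 − 1 − 1 = 12.

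This grouping is an assumption; the protocol does not state it.

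**3. How much the choice matters.** Let *v*, *f* and *m* be the numbers of vegetable, fruit and meat items answered yes (up to 3, 2 and 2). Each category with at least one yes contributes its full count to the 16-item score but only 1 to the merged score. The gap between the two scores is therefore

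max(*v* − 1, 0) + max(*f* − 1, 0) + max(*m* − 1, 0),

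which runs from 0 to 2 + 1 + 1 = 4 points.

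| Change in items 3 to 9 | 16-item sum | Merged score |
|---|---|---|
| None eaten → one vegetable, one fruit, one meat item | +3 | +3 |
| One vegetable item → two vegetable items | +1 | 0 |
| None eaten → all seven items (extreme) | +7 | +3 |

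The extreme ratio is 7/3 ≈ 2.3. It needs a diet that goes from none to all of seven groups in the recall period. The protocol gives no expected change in this score, so no typical effect can be calculated.

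**4. Whose diet.** No arithmetic applies here. The declared level is the individual, the participants are children under five, the respondent is the food preparer, and the question is put in the second person. The outside-home row, although labelled individual level, is also in the second person. The child is not mentioned anywhere in Appendix 4, and the child data sheet in Appendix 5 has no food-group items that would fill the gap.

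**The case against.** The strongest reply is that Appendix 4 is an unfinished template. It still contains a prompt to insert local foods. Section 3.14.5 plans a pre-test of the tools' adequacy, and section 3.14.7 plans an update before they are loaded onto the tablets. Section 3.15.2 has the mother or caregiver complete the individual questionnaire for each child, so proxy reporting is the intended model, and a trained interviewer might well ask about the child. Section 3.12.2.9 also cites two scoring guides that are not at hand, and a recoding rule often sits in a statistical analysis plan. If items are stored as listed, either score can be derived later without loss.

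Much of this stands. It makes the range conflict look like an omitted scoring step, and it means one cannot say flatly that the trial will fail to measure children's dietary diversity. It does not remove the conflict: the protocol states a range that its own rule and tool do not give, and no text tells interviewers to redirect the questions to the child. Section 3.2 does note that children of a household share a pot, but that is an argument for randomising households. It does not turn an adult's intake, including food eaten away from home, into the intake of a six-month-old.

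A reader might infer that this score is the trial's chief evidence that the dietary message changed intake. The protocol gives it no such role. More direct measures are planned: the monthly assessment of nutrients, enhancers and inhibitors (section 3.3), the 24-hour recall (section 3.12.2.4), and the dietary audit in the per-protocol definition (section 3.20).

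A reader might also infer that crediting tea and coffee under item 16 rewards what the intervention discourages. Table 3.2 asks only that they be kept apart from meals, so a food-group count that includes beverages does not contradict it.

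**Conclusion.** The point holds in two limited parts. As written, the score runs 0 to 16 against a stated 0 to 12. Read literally, the form records the food preparer's diet, although the score is declared to be at individual level in a trial of children.

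The size is modest. This is one secondary or intermediary measure, and neither the primary outcome nor the sample size depends on it. The merging choice moves an individual score by 0 to 4 points; the 7-against-3 contrast is an extreme and should not be read as the expected distortion. That figure rests on the assumed grouping of items 3–5, 6–7 and 8–9. Nothing suggests that the rule would differ between arms, so the documents do not support inferring bias in the treatment comparison from the scale conflict alone. The wording of the questions is the more pressing part, because it cannot be repaired once data are collected.

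**What to change.** Before fieldwork:

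- **Appendix 4.** Reword the opening prompt and the outside-home row to ask what the named child ate or drank. Alternatively, declare the score a household one, word the prompt accordingly, and correct the individual-level statements in section 3.12.2.9 and Table 3.1.
- **Section 3.12.2.9.** Either state that items 3–5, 6–7 and 8–9 each count once, giving 12 groups and a range of 0 to 12, or change the stated range to 0 to 16. Say that the outside-home row is not scored, if that is the intention. Apply one rule in both arms and at every visit.
- **Data capture.** Store all 16 answers separately so that the score can be recomputed.

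The cost is a few lines of wording and of scoring code, with no extra visits, samples or participants. The scoring rule could still be settled after data collection, but the wording of the questions could not.

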**Table 3.1 Baseline and Outcome measures, intermediary factors and time points**

| **Primary and Secondary outcomes** | | **Baseline** | **Week** | | **End-line** |
| --- | --- | --- | --- | --- | --- |
|  |  | **Week 0** | **4** | **8** | **Week 12** |
| **Primary outcome** | |  |  |  |  |
| 1 | Haemoglobin concentration | X |  |  | X |
|  | Anaemia prevalence | X |  |  | X |
| **Secondary Outcomes** | |  |  |  |  |
| **2** | **Anthropometry** |  |  |  |  |
|  | Weight | X |  |  | X |
|  | Length/Height | X |  |  | X |
|  | Mid Upper Arm Circumference | X |  |  | X |
| **3** | **Biochemical outcome** |  |  |  |  |
|  | Serum Ferritin | X |  |  | X |
|  | Serum Iron concentration | X |  |  | X |
|  | Serum transferrin saturation | X |  |  | X |
|  | Serum Vitamin B12 level | X |  |  | X |
|  | Serum folate | X |  |  | X |
|  |  |  |  |  |  |
| **4** | **Clinical Outcome** |  |  |  |  |
|  | ***General Examination*** |  |  |  |  |
|  | Oedema | X |  |  | X |
|  | Jaundice | X |  |  | X |
|  | Pallor | X |  |  | X |
|  | Skin and hair changes | X |  |  | X |
|  |  |  |  |  |  |
| **5** | **Dietary recall and quantification** |  |  |  |  |
|  | 24 hour dietary recall | X |  |  | X |
|  | Enhancers of iron in diet | X | X | X | X |
|  | Inhibitors of iron in diet | X | X | X | X |
| **6** | **Household food insecurity access scale (HFIAS)** | | |  |  |
|  | Household food insecurity | X |  |  | X |
| **7** | **Household dietary diversity score (HDDS)** |  |  |  |  |
|  | Administered at individual level | X | X | X | X |
| **8** | **Household Questionnaire** |  |  |  |  |
|  | Demographic data | X |  |  |  |
|  | Socioeconomic status | X |  |  |  |
| **9** | **Adherence to Study medication** |  | **X** | **X** | **X** |

